## Abstract

**Background:**

Pulmonary rehabilitation (PR) has demonstrated patients’ physiological and psychosocial improvements, symptoms reduction and health-economic benefits whilst enhances the ability of the whole family to adjust to illness. However, PR remains highly inaccessible due to lack of awareness of its benefits, poor referral and availability mostly in hospitals. Novel models of PR delivery are needed to enhance its implementation while maintaining cost-efficiency. We aim to implement an innovative community-based PR programme and assess its cost-benefit.

**Methods:**

A 12-week community-based PR will be implemented in primary healthcare centres where programmes are not available. Healthcare professionals will be trained. 73 patients with CRD and their caregivers (dyads patient-caregivers) will compose the experimental group. The control group will include dyads age- and disease-matched willing to collaborate in data collection but not in PR. Patients/family-centred outcomes will be dyspnoea (modified Medical Research Council Questionnaire), fatigue (Checklist of individual strength and Functional assessment of chronic illness therapy – fatigue), cough and sputum (Leicester cough questionnaire and Cough and sputum assessment questionnaire), impact of the disease (COPD Assessment Test), emotional state (The Hospital Anxiety and Depression Scale), number of exacerbations, healthcare utilisation, health-related quality of life and family adaptability/cohesion (Family Adaptation and Cohesion Scale). Other clinical outcomes will be peripheral (biceps and quadriceps-hand held dynamometer, 1 or 10 repetition-maximum) and respiratory (maximal inspiratory and expiratory pressures) muscle strength, muscle thickness and cross sectional area (biceps brachialis, rectus femoris and diaphragm-ultrasound imaging), exercise capacity (six-minute walk test and one-minute sit to stand test), balance (brief-balance evaluation systems test) and physical activity (accelerometer). Data will be collected at baseline, at 12 weeks, at 3- and 6-months post-PR.

Changes in the outcome measures will be compared between groups, after multivariate adjustment for possible confounders, and effect sizes will be calculated. A cost-benefit analysis will be conducted.

**Discussion:**

This study will enhance patients access to PR, by training healthcare professionals in the local primary healthcare centres to conduct such programmes and actively involving caregivers. The cost-benefit analysis of this intervention will provide an evidence-based insight into the economic benefit of community-based PR in chronic respiratory diseases.

**Trial registration:**

The trial was registered in the ClinicalTrials.gov U.S. National Library of Medicine, on 10th January, 2019 (registration number: NCT03799666).

**Electronic supplementary material:**

The online version of this article (10.1186/s12889-019-7045-1) contains supplementary material, which is available to authorized users.

## Background

Respiratory diseases represent five of the thirty most common causes of death worldwide [1, 2] and account for more than 10% of all disability-adjusted life-years [1]. It is known that these conditions impact on economic and social systems [3] but most importantly, cause enormous challenges for individuals and respective families. These patients experience disabling symptoms (including dyspnoea, fatigue, cough, sputum, anxiety and depression), limitation in their activities of daily life and social/family interactions, exercise intolerance, low physical activity levels and impairments in their quality of life [4–19]. Caregivers provide invaluable support to these patients, i.e., emotional/spiritual (e.g., someone to whom they can talk to), physical/practical (e.g., dressing, mobility assistance, medication check, overnight vigilance) and social and financial [20, 21]. Although they report positive experiences, negative impacts and specific needs directly related to their role have also been widely acknowledged [20–25]. However, very little has been done to support caregivers and there is lack of interventional studies [20, 21]. Pulmonary rehabilitation (PR) has been proposed as a possible response [21, 23, 26] since it could actively involve the family system within care delivery [27].

PR is a comprehensive intervention, which includes exercise training, education and behaviour change, to improve patients’ physical and psychological wellbeing and to promote their long-term adherence to health-enhancing behaviours [28]. In patients with chronic respiratory diseases (CRD) (chronic obstructive pulmonary disease [COPD], interstitial lung disease, bronchiectasis, cystic fibrosis, asthma, pulmonary hypertension, lung cancer), PR has demonstrated physiological and psychosocial improvements, symptoms reduction and health economic benefits [10, 29–37]. It has also shown to enhance the ability of the whole family to cope and psychosocially adjust to illness [27]. Given its benefits, PR has been proposed to be part of the standard care offered to patients with CRD [10, 28]. However, it continues to be highly inaccessible [10]. Patients lack awareness of its benefits, there is poor referral from healthcare professionals and programmes are mostly hospital-based and directed at patients with COPD at advanced stages [28, 38]. Therefore, it has been acknowledged that several steps are needed to increase access to PR, such as: i) enhancing accessibility of the existing programmes; ii) increasing the number of programmes especially in the community; iii) developing and validating novel models to deliver sustainable PR; iv) increasing PR reimbursement and payer acceptance; v) exploring its cost-benefit; vi) promoting maintenance of long-term results and vii) identifying those who should be prioritised [28, 38]. This study will address some of these steps. It is hypothesised that community-based PR, directed to patients with several CRD, at all grades of the disease, and involving different local stakeholders (i.e., healthcare professionals, patients, caregivers, decision-makers and the local community) may turn PR more accessible, sustainable and cost-effective.

## Methods

### Aims

The main goal of this project is to implement an innovative community-based PR programme and assess its cost-benefit. The primary objectives are to:1.1.Investigate the short- and medium-term effects of community-based PR programmes, implemented with minimal resources and with local healthcare professionals, in patients and caregiver’s health-related quality of life;1.2.Investigate the cost-benefit of the community-based PR programmes on acute exacerbations and healthcare utilisation, to determine whether the intrinsic perceived social value of such programmes have identifiable benefits and, consequently, measurable economic value for society.

The following secondary objectives will be addressed:2.1To explore the short- and medium-term effects of community-based PR programmes on patients and caregivers’ symptoms, impact of the disease, family adaptability/cohesion, peripheral and respiratory muscle strength, exercise capacity, balance and physical activity.2.2To explore differences between patients and caregivers’ who participate and those who did not participate in community-based PR programmes in relation to dyspnoea, fatigue, cough, impact of the disease, emotional state, health-related quality of life, number of exacerbations, healthcare utilization, family adaptability/cohesion, peripheral and respiratory muscle strength and thickness, exercise capacity, balance and physical activity.2.3To explore associations between patients and caregivers’ outcomes of dyspnoea, fatigue, cough, impact of the disease, emotional state, number of exacerbations, healthcare utilisation, family adaptability/cohesion, peripheral and respiratory muscle strength and thickness, exercise capacity, balance and physical activity, pre-post community-based PR programmes.2.4To investigate the short-term effects of community-based PR programmes on patients’ peripheral muscle (quadriceps and biceps) and diaphragm thickness, cross sectional area, echointensity and motion measured resorting to ultrasound imaging.

### Study design, setting and recruitment

A real-world non-randomised controlled study conducted in the community has been designed. Coordinators of primary healthcare centres will be approached in an arranged meeting to explain the study and those interested to participate will be asked to identify the multidisciplinary team available in their primary healthcare centre. Indication for the minimum staff required will be provided, i.e., a physician, a physiotherapist and a nurse; however, emphasis on the importance to include other professionals (e.g., nutritionist, psychologist, social worker), if available, will be given, following the international recommendations [28, 39, 40]. General practitioners and/or pulmonologists will identify eligible stable patients with a CRD (e.g., COPD, asthma, asthma-COPD overlap, interstitial lung disease, etc.) and their caregivers, and explain the study. Only patients and caregivers with interest in participating will be contacted by the researchers. A meeting will then be arranged to provide written and oral information about the study and collect the informed consent (Additional file 1). The researchers also explained that all data would be kept in databases password protected, using codes and their names would never be disclosed, ensuring the confidentiality and anonymity of all data. Two groups will be composed, experimental (EG) and control (CG). The EG will include patients and caregivers wanting to participate in a 12-week community-based PR programme and the CG will include those age- and disease-matched willing to collaborate in data collection but not in the PR programme. Recruitment started in January 2019, with final data collection expected to be completed in December 2019.

### Patient and public involvement

Patients and public were not directly involved in the study design or recruitment in this study however, authors were informed about their needs, preferences and expectations, as well as on the outcomes by recent published papers of the research team, and took those into consideration when designing the study [41, 42].

### Eligibility criteria

Patients will be eligible if they are diagnosed with a CRD [43, 44] and clinically stable in the previous month (i.e., no hospital admissions, exacerbations or changes in medication for the cardiorespiratory system). Exclusion criteria will be the presence of any clinical condition that can preclude participants of being involved in the community-based PR programme, such as, signs of cognitive impairment (e.g. dementia) or presence of a significant cardiovascular (e.g. symptomatic ischaemic cardiac disease), neurological (e.g. neuromuscular dystrophy disease) or musculoskeletal disease (e.g. important kyphoscoliosis). Caregivers will be included if they are: ≥18 years old and living with or providing physical/supportive care to the patient, and excluded if they are unable to cooperate.

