### Data collection

Sociodemographic (age, sex, educational level, marital and working status), anthropometric (height and weight to calculate the body mass index) and general clinical data (long-term oxygen, non-invasive ventilation, medical history, comorbidities to calculate the Charlson Comorbidity Index [45] and medication) will first be collected with a structured questionnaire to characterise the sample and will be followed by a lung function test with spirometry [46].

The primary outcome measure will be health-related quality of life, assessed with the St. George Respiratory Questionnaire (SGRQ) [47] in patients and with the World Health Organization Quality of Life Bref Questionnaire [48, 49] in caregivers. The number of acute exacerbations, healthcare utilisation costs and collateral costs (e.g. transport costs, work absence costs, sickness benefits) will also be collected to conduct the cost-benefit analysis [50].

In addition, the following secondary outcomes will be assessed: symptoms of dyspnoea (modified Medical Research Council Questionnaire [mMRC]) [51], fatigue (Checklist of individual strength [CIS-20]) [52] and Functional assessment of chronic illness therapy – fatigue [FACIT-F]) [53, 54], cough and sputum (Leicester cough questionnaire [LCQ] [55] and Cough and sputum assessment questionnaire [CASA-Q]) [56], impact of the disease (COPD Assessment Test [CAT]) [57, 58], emotional status (The Hospital Anxiety and Depression Scale [HADS]) [59, 60], Family Adaptation and Cohesion Scales [FACES-IV]) [61, 62], peripheral (biceps and quadriceps with the hand held dynamometer, 1 [1-RM] or 10 [10-RM] repetition-maximum) [63, 64] and inspiratory and expiratory muscle strength (respiratory pressure meter) [65], exercise capacity (six-minute walk test [6MWT] and one-minute sit to stand test [1-min STS]) [66, 67], balance (brief-balance evaluation systems test [Brief-BESTest]) [68] and physical activity (accelerometer) [14]. Peripheral muscle (rectus femoris and biceps brachialli) and diaphragm thickness, cross sectional area [69, 70] and echointensity [71], excursion and M-Mode Index of Obstruction (MIO) [72–74], will be measured with ultrasound images – ImageJ and Matlab software. Global rating of change scale [75] for fatigue, cough, sputum, peripheral and respiratory muscle strength and balance will also be collected.

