Data will be collected from patients and caregivers at baseline, at 12 weeks and at 3- and 6-months post-PR. Ultrasound imaging will only be collected at baseline and at 12 weeks in patients from the experimental group. Additional file 2 provides an overview of enrolment, intervention and outcomes to be assessed in each time point.

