### Data management and statistical analysis

All variables will be processed in IBM SPSS or MS Excel software. Descriptive statistics, including frequencies, means and standard deviations, medians and interquartile ranges, will be used as appropriate. Short- and medium-term effects of the community-based PR programmes will be verified using paired t-test or Wilcoxon signed-rank tests, accordingly to data normality. Mean scores of continuous variables will be compared between patients and their caregivers using independent samples t-test or Mann Whitney U test, depending on the variable distribution. Pearson correlation coefficient [91] and Bland and Altman plots [92] for continuous variables and Cohen’s k [93] for categorical variables, will be applied to study the relationship and agreement between patients and caregivers. Relationships between variables will be explored with inferential, correlational and univariate/multivariate analyses in SPSS. Differences between the EG and CG at different time points will be assessed using a two-way ANOVA with repeated measures (continuous data), Kruskal-Wallis (ordinal data) and Chi-square or Fisher exact probability tests (nominal data). If missing data is found during the study follow up, the generalized estimating equation’ models will be applied. This method is an extension of generalized linear models to longitudinal data which permits the inclusion of time-dependent variables and the analysis of incomplete data (without imputing missing data), common in longitudinal health studies [94]. A significance level of 0.05 will be used.

Whenever possible, minimal clinically important differences (MCID) will be established, following the current recommendations to integrate both anchor-based and distribution-based approaches [95, 96]. The final MCID for each measure will be pooled using MetaXL 5.3 (EpiGear International, Queensland, Australia), with the input data being the MCID generated by each anchor- and distribution-based method and, when appropriate, the respective confidence interval. A quality effects model [97] will be used and anchor-based methods will weigh more than distribution methods (i.e., 2/3 against 1/3) [98].

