A cost-benefit analysis will be conducted to determine the economic value of the perceived social value of community-based PR programmes. This analysis allows for the aggregation of both health and non-health benefits and costs of the PR programme and provides useful and quantifiable information [99, 100], not only for patients and health care institutions, but also for decision makers [101].

Focusing on the frequency and length of exacerbations, healthcare utilisation costs and quality of life gains, along with several indirect costs and benefits associated with PR implementation, including productivity loss of patients and caregivers who provide assistance, working, transportation costs, administrative costs, opportunity costs, sickness benefits payed to the patient or professional training and recruiting costs, three complementary data analysis will be held: cost:-effectiveness, −utility and -benefit.

As recent studies on COPD have demonstrated, it is suitable for cost-effectiveness analysis to rest on the ratio *incremental cost per exacerbation/healthcare utilisation avoidance* [102] aiming to compare relative costs and outcomes of PR. Then, to assess the expected impact on patients’ health-related quality of life, cost-utility analysis computes the measures of quality adjusted life years (QALY) [103] and healthy years equivalents (HYEs) [104] and determines the incremental cost per QALY/HYE gained. Finally, to account for the monetary translation of positive and negative effects of community-based PR programmes, cost-benefit analysis will be performed by determining the measures of net present monetary benefit and economic internal rate of return [105], along with a sensitivity analysis to control for the uncertainty on the assessment of costs and benefits associated to the community-based PR programmes [106, 107].

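### The event-free month required at entry distorts any change from baseline in exacerbation and admission counts, and the named tests make no allowance for it

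*Protocol article*

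**What the plan says.** - **Entry rule** (Eligibility criteria): patients must be "clinically stable in the previous month (i.e., no hospital admissions, exacerbations or changes in medication for the cardiorespiratory system". No separate rule is given for controls.
- **Outcome** (Data collection): "The number of acute exacerbations, healthcare utilisation costs and collateral costs" are collected for the cost-benefit analysis. The general visit schedule is "Data will be collected from patients and caregivers at baseline, at 12 weeks and at 3- and 6-months post-PR".
- **Change** (Abstract, Methods): number of exacerbations and healthcare utilisation are listed among the patient and family outcomes. Changes in the outcomes are to be compared between EG and CG with multivariate adjustment.
- **Tests** (Data management and statistical analysis): "Short- and medium-term effects of the community-based PR programmes will be verified using paired t-test or Wilcoxon signed-rank tests", and "Differences between the EG and CG at different time points will be assessed using a two-way ANOVA with repeated measures (continuous data" plus tests for ordinal and nominal data. Generalized estimating equations are reserved for the case of missing data. No count family, time offset or rate is mentioned, and event counts are not exempted from either test.
- **Economic use** (same section): the cost-effectiveness ratio is an incremental cost per exacerbation or healthcare contact avoided, "aiming to compare relative costs and outcomes of PR".
- **Groups** (Study design, setting and recruitment): EG and CG form by willingness to take part in PR; controls are matched on age and disease.

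**The concern.** The entry rule empties the last month of any look-back that ends at entry. Follow-up carries no such restriction. A count before entry and a count after it are therefore not comparable, even over windows of equal length. If the look-back is longer than the follow-up interval, unequal time is added on top.

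The artefact applies in full to exacerbations and hospital admissions, which the rule names. It applies only in part to other healthcare use, such as routine visits, which the rule does not exclude.

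These events feed primary objective 1.2. An artefact of the entry rule could be read as harm or benefit of PR, depending only on the look-back chosen.

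**Working it through.** The plan gives no figure for exacerbations, so there is none to reproduce.

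**Inputs from the Protocol article**
- Event-free period: one month, taken as 365.25/12 = 30.44 days.
- First follow-up interval: 12 weeks = 84 days = 2.76 months.
- Whole follow-up: 12 weeks plus 6 months = 84 + 182.6 = 266.6 days.

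**Assumptions (not in the article)**
- A constant event rate λ per patient-year and no PR effect.
- A look-back of L months ending at entry, with L varied.

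**Step 1: raw counts within one group**

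Expected baseline count = λ(L − 1)/12. Expected 12-week count = λ × 84/365.25 = 0.230λ. In the ratio, λ cancels. For λ = 1:

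| Look-back | Baseline | First 12 weeks | Follow-up/baseline |
|---|---|---|---|
| 1 month | 0.000 | 0.230 | undefined |
| 12 weeks | 0.147 | 0.230 | 1.57 |
| 3 months | 0.167 | 0.230 | 1.38 |
| 6 months | 0.417 | 0.230 | 0.55 |
| 12 months | 0.917 | 0.230 | 0.25 |

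A 12-month count against the whole follow-up gives (266.6/365.25)/0.917 = 0.730/0.917 = 0.80, an apparent 20% fall. The 12-week raw counts balance only when (L − 1)/12 = 84/365.25, so L = 1 + 2.76 = 3.76 months. That is 12 weeks plus the stability month.

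**Step 2: rates instead of counts**

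The observed baseline rate is λ(L − 1)/L, which is too low by 1/L: 36% at 12 weeks, 33% at 3 months, 17% at 6 months and 8% at 12 months. Dividing by time helps but does not remove the error unless the stability month is left out.

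**Step 3: false-positive rate of the paired test**

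The simulation used gamma-Poisson counts (dispersion 0.7), conditioned on no event in the last month. It assumed 73 patients per group, λ of 0.5, 1 and 2 per year, no PR effect, and 1,000 runs per setting. The within-EG paired t-test at 5% rejected in:
- 92–100% of runs with a 1-month look-back
- 11–32% with 12 weeks (apparent rise)
- 27–75% with 6 months (apparent fall)
- 97–100% with 12 months (apparent fall)

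With the same windows and the same rate in both groups, the EG–CG difference in change averaged about zero (−0.009 to 0.011) and rejected in 3.6–6.2% of runs.

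**Step 4: unequal underlying rates**

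With no PR effect, the EG–CG difference in raw change is (λ_EG − λ_CG) × [0.230 − (L − 1)/12]. Take assumed rates of 1.5 in EG and 1.0 in CG:
- 12-month look-back: 0.5 × (0.230 − 0.917) = −0.34, a false 0.34 exacerbations avoided per EG patient.
- 12-week look-back: 0.5 × (0.230 − 0.147) = +0.04, a small false excess.

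The within-group ratios still agree (0.25 in both groups at 12 months). The error therefore arises from subtracting raw counts, as repeated-measures ANOVA does.

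**The case against.** **The paired test may not be meant for these outcomes.** The phrase about short- and medium-term effects belongs to objectives 1.1 and 2.1, and neither lists exacerbations or healthcare use. This stands in part: assigning the paired test to event counts is an inference. But the analysis section does not limit the test by outcome, and the Abstract includes both outcomes among those whose changes are compared.

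**The control group removes the artefact.** One eligibility rule covers all patients, objective 2.2 compares exacerbations between participants and non-participants, and the cost ratio needs a comparator. This stands when windows and rates are alike, as Step 3 shows. It does not stand when rates differ (Step 4). The groups select themselves, and exacerbation history is not a matching variable. The Abstract's multivariate adjustment might include it, but does not say so.

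**The look-back may be fixed elsewhere.** A reader might infer that the trial has no common window. The documents do not support that. The article is silent, refers the outcome schedule to Additional file 2, which is not shown, and condenses a fuller protocol. The point does not rest on a missing window.

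**Rates may already be intended.** The economic paragraph opens "Focusing on the frequency and length of exacerbations", which could mean events per unit of time. Even so, a rate that counts the stability month stays too low (Step 2).

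A reader might also infer from objective 2.3, with its "pre-post community-based PR programmes", that a before-after test of exacerbations is planned there. It is not: that objective concerns associations between patients' and caregivers' outcomes.

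**Conclusion.** The point holds in limited form. The entry rule and the unrestricted tests are both stated, and together they make a within-group change in raw exacerbation or admission counts uninterpretable. With no PR effect, the apparent change runs from a 57% rise (12-week look-back) to a 75% fall (12-month counts against 12-week counts). The direction cannot be told from the article. These percentages assume a constant rate and a look-back ending at entry; they do not depend on the event rate. The rejection rates in Step 3 do depend on the assumed rates, dispersion and group size.

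A reader might infer that the EG–CG comparison is also invalid, or that objective 1.2 will monetise a within-group change. Neither is supported. The between-group change is unbiased under equal windows and rates, and no passage says that a single-group change enters the cost ratio. What remains is that equality of rates is not secured by this design, and that a better method is cheap. The change should be made, but the issue does not undermine the trial as a whole.

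**What to change.** In Data management and statistical analysis:
1. Exclude exacerbations and healthcare utilisation from the paired within-group tests.
2. Analyse them, including for objective 1.2, as EG versus CG event rates over follow-up person-time, using a count model with a time offset.
3. Include the baseline event rate as a covariate. Take it over one look-back common to both groups, with the stability month left out of both the events and the time.

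In Data collection, state that look-back, or point to the place where it is fixed.

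**Cost:** analysis and questionnaire wording, with no extra visit. The baseline rate will rely on records or recall of events before the stable month. Recruitment began in January 2019, so for patients already enrolled it may have to be filled in afterwards. Adjusting for the baseline rate reduces confounding by self-selection but does not remove it.
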